### Participants

The target participants for this study are general and orthopaedic surgeons, and their registrars who consult out of the elective outpatient clinic in a major tertiary hospital in a regional city in Australia. The clients presenting to this clinic are ambulatory, non-admitted clients. While this group may be seen as a representation of the general community-dwelling population, research indicates that patients presenting to hospital clinics are more likely to have higher rates of chronic disease than the general population [3, 4, 7].

As there are only a limited number of surgeons (general and orthopaedic) (*n* = 20) and registrars (*n* = 11) operating out of the study hospital, we will offer participation to all of these practitioners. Recruiting all surgeons and registrars consulting out of the hospital will increase the potential sample size, and provides a participant sample with differences in career stage and level of training. In qualitative description, the methodology seeks to gather enough data to saturate the explanation [27, 28]. Interviews will be continued until no interviewees are providing new information, and data saturation is determined [30]. If it is deemed that theoretical saturation is reached prior to full recruitment, then recruitment will discontinue [25, 27, 30].

We will recruit participants from one study site only. We have chosen to recruit participants from one study site only due to the heterogeneity that exists between hospitals in terms of infrastructure, clinical practice and resources, as well as broader contextual factors that may differ between areas serviced by hospitals such as the availability of, and access to, local preventative health providers and programs [31]. This study is part of a broader body of work, investigating health promotion in non-admitted secondary care patients. We have already undertaken a clinical trial investigating behaviour change interventions for non-admitted secondary patients in a single-hospital setting (ANZCTR trial id: ACTRN12616001331426). This proposed mixed-methods study aims to fill the gap in knowledge pertaining to surgeons’ actual involvement in the practice of health promotion in an ambulatory care setting; these results can be used in the design of subsequent clinical trials involving surgeons screening and recruiting secondary care patients for behaviour change interventions.

### Recruitment

An email will be sent to all potential participants by their head of department, explaining the rationale for the study and the inherent requirements. The email will explain that participants can take part in the clinician survey, the interview, or both. The email will contain a link to the electronic version of the clinician survey. The email will also inform participants that a hard copy version of the clinician survey is available if this is preferred. The email will contain contact details for the research team for those individuals who would like more information. To assist with completion rates [32], two subsequent reminder emails with attached clinician survey link will be sent out through the same electronic channel, at four-weeks and eight-weeks post initial email.

Individual participants will be approached to discuss involvement in the interviews, and where interested, a time will be arranged with each clinician to undertake the interview. Every effort will be made to allocate sufficient time in the interview to discuss informed consent and undertake the interview. Participants will be given a Participant Information and Consent Form to complete prior to undertaking the interview. Where appropriate, and to coordinate scheduling, the coordination of the interview times may be facilitated through the personal assistants of the surgeons. To facilitate the development of interview topics and question design, we aim to have at least 5 clinician surveys completed and analysed before undertaking any interviews.

### Analyses

#### Clinician survey

Consistent with published literature utilising this survey [18, 23], the relationship between the dependent variables (clinician practices) and independent variables (confidence, knowledge and attitudes) will be analysed. Due to the small sample of clinicians available for recruitment, dependant variables will be recorded as low, moderate or high. Low implementers will be defined as clinicians with screening and intervention scores, across all risk factors, in the first quartile. High implementers will be defined as clinicians with screening and intervention stores, across all risk factors in the fourth quartile. Given the relatively small sample size, a Generalized Estimating Equation will be used to estimate the parameters of a generalized linear model with a possible unknown correlation between outcomes [33]. The generalized estimating equation procedure extends the generalized linear model to allow for analysis of repeated measurements or other correlated observations [33]. Generalized estimating equations allows for the highlighting of moderators that do not directly correlate with the outcome of interest, but influence other related factors [33–35]. Analysis of the surveys will be used to offer exploratory themes, questions and question-related probes for the semi-structured interviews.

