**Methods:**

A mixed methods study will be conducted, guided by the principles of sequential explanatory design. Quantitative results from a clinician survey will be followed by in-depth, semi structured interviews to explore findings in more depth through qualitative analysis. We will recruit from general and orthopaedic surgeons and registrars in a major tertiary hospital in a regional city in Australia (n ≈ 31). Data will be collected, independently coded and analysed using a qualitative descriptive approach. Quantitative and qualitative results will be merged during interpretation to provide complementary perspectives of interrelated contextual factors that influence health promotion activities amongst hospital surgeons.

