### Clinician survey

Surgeons will be invited to complete a short 17-item self-administered clinician survey to assess health behaviour risk factor management, perceived knowledge, confidence and attitudes towards preventative health (Additional file 1). The clinician survey asks respondents to report on proportions of clients seen over a recent period who they: (1) asked about smoking, nutrition, alcohol and physical activity; (2) assessed for readiness to change; (3) provided verbal and written advice on these risk factors and; (4) referred to other services for support in changing risk factors. These clinician practices are the dependent variables. The clinician survey also questions the participants about their knowledge and confidence in screening and managing each risk factor. In addition, attitudinal measures will be included for: (1) the clinicians’ opinion on the perceived effectiveness of the interventions; (2) the perceived importance of the intervention for the clients they see; (3) perceived work priority; and (4) perceived acceptability on the part of the client of raising the topic of lifestyle risk factors. The answers to these questions constitute the independent variables. All clinician survey items are measured on a 5-point Likert scale. The clinician survey has been adapted with permission from a previously developed instrument used to assess health behaviour risk factor management practices and capacity in community dwelling participants [18, 23].

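### The small sample is given as the reason for a GEE and for quartile grouping, but neither helps with at most 31 clinicians and about 12 uncombined candidate predictors

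*Protocol article*

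**What the plan says.** In Methods/design, Clinician survey, the practice items are the dependent variables. They cover asking, assessing readiness to change, advising and referring. The risk factors come from the first of them: clients "asked about smoking, nutrition, alcohol and physical activity". On the predictor side, "The clinician survey also questions the participants about their knowledge and confidence in screening and managing each risk factor". Four attitude measures follow: effectiveness, importance, work priority and acceptability to the client. The answers to all these questions are declared the independent variables.

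The Participants section describes the pool as a "limited number of surgeons (general and orthopaedic) (*n* = 20) and registrars (*n* = 11"), and the Abstract gives the total as about 31. Under Recruitment, people may take the survey, the interview or both, so 31 is a ceiling.

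Analyses, Clinician survey, relates practices to "independent variables (confidence, knowledge and attitudes"). It cites the small number of clinicians as the reason for coding practice as low, moderate or high, with the first and fourth quartiles as the outer groups. It cites the small sample again as the reason for the GEE, adding that the method accommodates correlated outcomes. It ends: "Analysis of the surveys will be used to offer exploratory themes, questions and question-related probes for the semi-structured interviews".

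**The concern.** Two design decisions rest on a rationale that runs the wrong way. A GEE deals with correlated observations within a clinician. It adds no clinicians, and its usual robust (sandwich) variance relies on having many independent clusters. A small sample is therefore a reason for caution with a GEE. Cutting a score at its quartiles also leaves less information in a sample that is already short of it.

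The candidate predictor list is long for this number of people, and the analysis text says nothing to shorten it. If the ordinary robust tests are used, apparent links between attitudes or confidence and practice will be declared too often. The Participants section says the results can feed the design of later trials, and the Discussion says they might guide policy, so overconfident associations would matter beyond this study.

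**Working it through.** **Inputs from the protocol article**
- Clinicians: 20 surgeons + 11 registrars = 31, which reproduces the Abstract's figure. It is a headcount; no power calculation, significance level or response rate is given.
- Candidate predictors: 2 (knowledge, confidence) × 4 risk factors + 4 attitude measures = 12. The count is inferred from the text, because the instrument (Additional file 1) is not shown.
- Outer outcome groups: 31 / 4 = 7.75, so about 8 clinicians each at full response.

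**Assumptions:** 5% two-sided level, no true association, uncorrected robust variance with a normal reference. The protocol names neither a level nor a variance estimator.

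**Nominal error if each test were valid and independent**
- 12 predictors: 1 − 0.95^12 = 0.46
- 6 predictors: 1 − 0.95^6 = 0.26
- 3 predictors: 1 − 0.95^3 = 0.14

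**Simulated error of the ordinary robust test** (null data, one outcome per clinician, predictors correlated at 0.3)

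| Predictors entered jointly | Per predictor, n = 31 | At least one, n = 31 | Per predictor, n = 20 |
|---|---|---|---|
| 12 | 18% | 81% | 32–33% |
| 6 | 12% | 48% | 17–19% |
| 3 | 10% | 25% | 13–15% |

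A GEE fit with independent five-point predictors and the three-level outcome gives nearly the same at n = 31: 17% and 82% with 12 predictors, 10% and 27% with three. If the four risk factors are stacked as four rows per clinician (six predictors, within-clinician correlation assumed 0.5), it gives 8.5% per predictor and 40% for at least one.

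**What each correction contributes.** Under the same robust test, going from 12 predictors to three lowers the per-predictor error from 18% to 10%. A t-based test with three predictors brings it to 5%, and the chance of at least one false positive to 14%. Reducing predictors alone is not enough.

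**Cost of the quartile grouping.** Take a normally distributed score coded −1, 0, 1 at its quartiles (±0.6745). Covariance with the score is 2 × 0.3178 = 0.636, and the variance of the code is 0.5. The squared correlation is 0.636² / 0.5 = 0.81. For weak linear associations, 31 clinicians then carry the information of about 31 × 0.81 = 25. If the top quartile is modelled against the rest with 12 predictors, the null data were perfectly separable, so that a logistic fit has no finite estimates, in 46% of runs at n = 31 and 96% at n = 22 (an assumed 71% response). With three predictors this did not occur at either size.

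**The case against.** The strongest reply is that the 12-predictor model is not in the text. The analysis section names three constructs, and three scores fit that wording. Stacking by risk factor also fits the reference to correlated observations, although defining implementer level across all risk factors points to one value per clinician. Scoring rules and small-sample corrections are often left to an analysis plan, which is not shown. All of this is fair, and it is why the figures are given for each reading. What it does not rescue is the stated rationale: the document itself gives small n as the reason for the GEE and for the grouping, and the uncorrected test is anticonservative on every reading.

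Two stronger inferences are tempting, and the document supports neither.
- A reader might infer that the model will largely fit noise. Even with all 12 entered in a linear model, the R² expected by chance at n = 31 is 12 / 30 = 0.40. It passes one half only at 24 or fewer respondents, and joint entry is not stated.
- A reader might infer that false leads will determine the interview topics. The survey-derived themes are called exploratory, the questions are open-ended, and the script is reviewed after each interview. Interviews may begin once five surveys are analysed, when a 12-predictor model cannot be fitted at all. A spurious lead can be dropped.

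The primary outcomes in the Discussion are also descriptive, and the limited number of participants is acknowledged there.

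**Conclusion.** The point holds as a flaw in the stated reasoning and an under-constrained model. Few clinicians is not a reason to choose a GEE or to group the outcome by quartile, and about 12 candidate predictors are left neither limited nor combined. With an uncorrected robust variance, the real error at full response is roughly two to three and a half times the nominal 5% per predictor (10% to 18%), and higher with fewer respondents. This rests on the inferred predictor count, an assumed 5% level, no true association, and the ordinary variance being used. The harm is moderate because the survey serves a descriptive and exploratory purpose, but the section should be corrected before the associations are analysed.

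**What to change.** In Analyses, Clinician survey:
- Remove the small-sample justification for the GEE. Keep the GEE only where several correlated outcomes per clinician are modelled, and say so.
- Analyse the screening and intervention score as a continuous variable. Quartile groups can remain as description.
- Use a small-sample method: t-based intervals where there is one score per clinician, or a bias-corrected robust variance with a t reference where there are several rows.
- Prespecify a few construct scores for any joint model: mean knowledge, mean confidence, and an attitude score if the four attitude items can reasonably be combined. Show item-level results descriptively.
- Report effect sizes with intervals and label the associations exploratory.

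The cost is analysis wording only, with no extra data. Risk-factor-specific predictors would be described rather than modelled. Merging the four attitude measures is a real trade-off, since they are distinct, and it may reduce comparability with the published uses of the instrument that the section says it follows.

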## Discussion

Hospitals play an important role in sick care, the provision of rehabilitation services, the promotion of health, and the prevention of disease [4]. These activities have been core components of hospital work; however, the increasing prevalence of lifestyle-related chronic diseases necessitates a more expanded scope, and standardised provision of initiatives to enable clients to take an active role in preventative health and chronic disease management [5, 7, 8]. This requires the reorientation of health care facilities to integrate health promotion, disease prevention and rehabilitation services in curative care [17]. Hospitals can have a strong influence on health behaviour, with patients demonstrating more responsiveness to health advice in situations when they are experiencing ill-health [39]. A fundamental necessity towards integrating health promotion in hospital settings is strong leadership at different levels of hospital governance [7, 8]. This leadership is epitomised by hospital surgeons, influential figures within both clinical settings, and by extension, hospital organisational culture and practice [16, 40]. Surgeons are seen as the predominant authoritative source of advice and expertise on health issues, having influential roles in both clinical and administrative structure [7, 10, 39]. In spite of this, information regarding the professional practice, and the opinions of these exemplars of clinical practice pertaining to preventative health are absent from the literature.

The primary outcomes of this study will be to: (1) identify what health promotion activities surgeons carry out in public hospitals, and (2) explore the attitudes of surgeons towards preventative health practice. The depth of insight gained from the study of these highly professionalised clinical groups will offer a distinctive perspective on current practice, as well as the challenges of implementing effective health promotion into surgical practice. The findings from this study will offer insight into individual, institutional and contextual factors that influence surgeons’ decisions to participate in health promotion activities.

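### Grouping the practice scores at quartiles because the sample is small makes that sample effectively smaller, and the resulting labels are relative, not levels of activity

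*Protocol article*

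**What the plan says.** Under Methods/design, Clinician survey, the practice items are the dependent variables. "The clinician survey asks respondents to report on proportions of clients seen over a recent period" whom they asked, assessed, advised or referred, and "All clinician survey items are measured on a 5-point Likert scale".

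Under Analyses, Clinician survey, these outcomes are to be related to confidence, knowledge and attitudes with a generalized estimating equation. Before that they are grouped: "Due to the small sample of clinicians available for recruitment, dependant variables will be recorded as low, moderate or high". The cut-points follow: "Low implementers will be defined as clinicians with screening and intervention scores, across all risk factors, in the first quartile", and "High implementers will be defined as clinicians with screening and intervention stores, across all risk factors in the fourth quartile". The section names no absolute threshold and no reference distribution for the quartiles. It does not say that the ungrouped score will also be analysed.

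The Participants section gives 20 surgeons and 11 registrars, all to be invited. The Discussion names as the first primary outcome to "identify what health promotion activities surgeons carry out in public hospitals".

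**The concern.** A small sample is a reason to keep every gradation of the outcome. Three groups treat all clinicians within a group as identical and discard the differences between them, so the association between practice and attitudes is estimated less precisely where there is least precision to spare.

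A quartile label also ranks a clinician against the other respondents. It carries no information on how often the activity takes place. If the labels were read as levels, a clinic where almost nobody counsels patients would still appear to have a group of high implementers.

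**Working it through.** **Inputs.** 20 + 11 = 31 clinicians, which reproduces the n ≈ 31 in the Abstract. The split is 25/50/25, from the quartile definitions. The protocol article states no response rate, significance level, power or effect size for the survey, so any such value below is an assumption.

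**Information kept, normal score.** Score the groups S = −1, 0, 1 with cuts at ±c, where c = z(0.75) = 0.6745.
- Cov(X, S) = 2·φ(c) = 2 × 0.3178 = 0.6356
- Var(S) = 0.25 + 0.25 = 0.5
- r = 0.6356 / √0.5 = 0.899, so r² = 0.808 and the loss is 19.2%
- Effective number: 31 × 0.808 = 25.0. To make up the loss, 31 / 0.808 = 38.4 clinicians would be needed.
- If only 16 responded (assumed): 16 × 0.808 = 12.9.

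**Sensitivity to the shape of the score.**
- Rank (proportional-odds) scale: 1 − (2 × 0.25³ + 0.5³) = 0.844, a loss of 15.6%.
- Uniform score: also 15.6%.
- t with 5 degrees of freedom: 28%. Exponential: 37%. Lognormal: 61%.
- Simulated sums of 16 five-point ratings at n = 31: 18% to 22%. The 16 ratings are an assumption (four practices by four risk factors), because the instrument is in an additional file that is not shown.

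**What this does to power.** Simulation at n = 31, two-sided 0.05, normal scores, with assumed correlations between practice and an attitude score:

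| Correlation | Full score | Three groups |
|---|---|---|
| 0.3 | 38% | 31% |
| 0.4 | 63% | 53% |
| 0.5 | 84% | 74% |
| 0.6 | 96% | 91% |

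**What the labels mean.** A quarter of 31 is 7.75, so each outer group holds about 8 clinicians. In the 16-rating simulation the average level of practice was moved from low to high, so that the upper-quartile mean item response went from 2.0 to 4.8 out of 5. The share labelled high stayed at 27% to 28% throughout (slightly above 25% because of ties and the small n). With an illustrative fixed cut, a mean item response of at least 4, the share over the same scenarios ran from 0.1% to 75%. The quartile label does not register a change that the original scale shows clearly.

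**The case against.** The survey is exploratory. It invites everyone available at one site, states no confirmatory hypothesis, and mainly feeds the interview questions. The Discussion already acknowledges the limited numbers. Losing about a fifth of the efficiency in such an analysis does not defeat either aim. This stands and limits the weight of the point. It does not rescue the stated reason, which is wrong at any sample size.

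Several stronger readings are tempting, but the document does not support them.
- *The first primary outcome will be reported only as low, moderate or high.* A reader might infer this, but the recoding is introduced for the association analysis. Nothing says that the item responses will be withheld, and routine descriptive tables may be left to a fuller document.
- *Exactly a quarter of surgeons are called high.* This needs sample quartiles of one pooled score. That is the natural reading, but no reference distribution is named. If external or scale-range quartiles were meant, the statement would not follow. If a clinician must be in the top quartile on every risk factor separately, the simulated share is 9% to 11%, roughly 3 of 31. The label is then still relative.
- *Ties make the group sizes arbitrary.* That could matter for a score of very few items. With 16 ratings and answers skewed low, the low group stayed between 26% and 32% of clinicians (5th to 95th percentile).
- *The grouping breaks, or preserves, comparability with earlier uses of the survey.* The article cites those studies for analysing the relationship between practice and attitudes and does not say how they presented scores, so neither claim can be made.

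**Conclusion.** The point holds in a limited form. The small-sample justification is backwards: grouping costs about 19% of the information if the score is roughly normal and the groups are equally spaced. The loss is about 16% for a uniform score or on a rank scale, and can be considerably more under strong skew. With full response, 31 clinicians count as about 25; with non-response the number falls in proportion. On the natural reading of the quartiles, about a quarter are labelled high regardless of absolute practice, so the labels cannot be used as evidence of how much health promotion takes place. The power figures rest on assumed correlations and an assumed 0.05 level. This should be fixed because a better analysis of the same data is available, but the study does not fail without it.

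**What to change.** In Analyses, Clinician survey:
- Remove the sentence that justifies grouping by the small sample.
- Use the full summed or mean practice score as a continuous or ordinal dependent variable in the association analysis.
- Describe activity levels from the original 5-point responses, by activity and risk factor.
- If low, moderate and high groups are kept to guide the interviews, use them descriptively only. State that they are relative to this sample, which distribution the quartiles come from, and whether the score is pooled over risk factors.

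The cost is a change of wording. No new data, items or participants are needed.

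### The low/moderate/high rule gives each clinician one label from two behaviours, can be read in more than one way, and leaves the planned GEE without within-clinician outcomes

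*Protocol article*

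**What the plan says.** The first Clinician survey section (Methods/design) lists four kinds of practice: asking about risk factors, assessing readiness to change, advising, and referring. It adds: "These clinician practices are the dependent variables".

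The Clinician survey section under Analyses says that the dependent variables, in the plural, will be recorded in three levels because few clinicians are available. Two definitions follow:

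- Low: "Low implementers will be defined as clinicians with screening and intervention scores, across all risk factors, in the first quartile".
- High: "High implementers will be defined as clinicians with screening and intervention stores, across all risk factors in the fourth quartile" (the word stores is evidently scores).

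No definition of moderate is given, and no rule covers a clinician whose two scores fall in different quartiles. The same section plans a GEE on the ground that outcomes may be correlated in an unknown way, and uses the survey analysis to shape the interview questions.

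Participants counts 20 surgeons and 11 registrars and says "we will offer participation to all of these practitioners". Recruitment says "participants can take part in the clinician survey, the interview, or both", so 31 is the most that can reply to the survey. The Discussion gives as the first primary outcome to "identify what health promotion activities surgeons carry out in public hospitals".

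**The concern.** The plan starts with several practices as outcomes and ends with one label per clinician. Three things follow.

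1. **The rule is not reproducible.** Two analysts working from the same sentence could form end classes of clearly different size from the same data.
2. **The label merges different behaviour.** Someone who often asks but seldom intervenes, someone who seldom asks but intervenes at an average rate, and someone in the middle on both can all end up as moderate. A predictor that acts on only one behaviour, such as confidence to counsel, is then diluted in the association analysis.
3. **The outcome does not fit the model.** A GEE chosen for correlated outcomes needs more than one outcome per clinician, and a single label supplies one.

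At stake is how useful the association analysis is, and with it part of what feeds the interview guide.

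**Working it through.** **Plan's own figure.** 20 surgeons + 11 registrars = 31, which agrees with the approximate total in the Abstract. The article gives no class sizes, no correlation between scores and no response rate.

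**Inputs.** n = 31 (Participants) as a ceiling; n = 20 replies as an assumption. Quartile cut-offs at 25% and 75% (Analyses). Correlation r between the screening and intervention scores is assumed, with a range of 0.3 to 0.7 and 0.9 as a high value. The two scores are taken as roughly bivariate normal.

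**Reading A, one combined score.** Expected end class = n × 0.25 = 31 × 0.25 = 7.75, so about 8 low, 8 high and 15 to 16 moderate. With 20 replies, 20 × 0.25 = 5 per end class.

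**Reading B, both scores in the extreme quartile.** Let p = P(Z1 ≤ z, Z2 ≤ z), with z the 25th percentile of the standard normal and correlation r. Expected end class = n × p, the same for low and high by symmetry. Moderate share = 1 − 2p.

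| r | p | Each end class, n = 31 | Each end class, n = 20 | Moderate share |
|---|---|---|---|---|
| 0.3 | 0.095 | 2.9 | 1.9 | 81% |
| 0.5 | 0.120 | 3.7 | 2.4 | 76% |
| 0.7 | 0.150 | 4.7 | 3.0 | 70% |
| 0.9 | 0.193 | 6.0 | 3.9 | 61% |

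Simulation with sample quartiles gives nearly the same means at n = 31: 3.1, 3.9 and 4.8 at r = 0.3, 0.5 and 0.7. At n = 20, the smaller end class holds 0 or 1 clinician in about 55%, 31% and 9% of samples at those correlations.

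**Clinicians moved to moderate under reading B.** Let d be the probability of opposite extremes, counting both directions: 0.068, 0.036 and 0.011 at r = 0.3, 0.5 and 0.7. The share that is extreme on exactly one score, and so coded moderate, is 1 − 4p − 2d plus d for those at opposite extremes, that is 1 − 4p − d in total for everyone extreme on at least one score yet moderate. This gives 0.55, 0.48 and 0.39, or about 17, 15 and 12 of 31.

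**Strongly discordant clinicians.** Screening in the top quartile with intervention in the bottom has probability d/2 = 0.034, 0.018 and 0.005, or about 1.1, 0.6 and 0.2 of 31. Under reading A, about 92%, 97% and over 99% of these would also be moderate.

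**Fit with the GEE.** Under A or B, each clinician contributes one label from one survey. The article names no other unit within which outcomes would be correlated. Separate screening and intervention outcomes would give two observations per clinician, which is the structure the model is meant for.

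**The case against.** The sentence never says that both scores, or each score, must qualify, so reading B cannot be treated as the settled rule. A reader might infer that it is, because two behaviours are joined by a conjunction and the noun is plural. One combined score fits the words as well and gives the 8/15/8 split that a quartile rule suggests. A third reading, each practice classified on its own score, fits the plural dependent variables and the GEE. On that view the fix is close to what was intended. This objection stands as to intent. It does not rescue the text, because the only definition given classifies clinicians and not practices.

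A reader might also infer that the first primary outcome is lost. The documents do not support that. The practices are collected as separate items, the three-level coding belongs to the association model, and item frequencies can still be reported. The interview questions draw on the survey analysis as a whole, not on this label alone.

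A further tempting inference is that the both-scores rule is what hides surgeons who ask but do not act. Those at full opposite extremes are only about 0 to 1 of 31 at r = 0.3 to 0.7, and a combined score would place nearly all of them in the middle too. Most of the 12 to 17 clinicians counted above are extreme on one score and mid-range on the other, for whom moderate is a defensible label. What remains is that any single label loses the distinction.

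Finally, the study is exploratory and acknowledges its small sample. That limits the consequence but does not make the rule clear.

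**Conclusion.** The point holds as an unclear outcome definition that does not match the plan's own dependent variables or model. It does not show that a both-scores rule was chosen.

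If both scores must qualify, each end class is about 3 to 5 of 31 instead of about 8. This rests on roughly normal scores, r between 0.3 and 0.7, and all 31 replying. At r = 0.9 it is about 6; with 20 replies and r of 0.3 to 0.7 it is about 2 to 3. None of these class sizes comes from the documents. On that reading the rule works against its stated reason, since classes adopted because the sample is small become smaller still.

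Two consequences do not depend on which single-label reading is right: asking and acting cannot be told apart in the association analysis, and the GEE has no within-clinician outcomes to correlate. The plan should be changed on this point.

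**What to change.** In the Clinician survey section under Analyses:

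- Derive a screening score and an intervention score for each clinician. Analyse them as scores or, if classes are kept, classify each on its own distribution and define moderate explicitly as the middle two quartiles of that score.
- Enter the two as correlated outcomes per clinician in the GEE, with an outcome-type term. Treat interactions between that term and the predictors as exploratory, since n is at most 31.
- Report the screening-by-intervention cross-tabulation, so that discordant patterns are visible and can be followed up in the interviews.
- Drop the single clinician label. If expected class sizes are quoted, give them as a range with the assumed correlation and number of replies.

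This changes analysis wording only and needs no new data. The small downside is two sets of estimates to report instead of one label per clinician.
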